#### Statistical analysis

All primary and secondary endpoints will first be analyzed on an intention-to-treat basis (all patients according to the assigned treatment groups), and secondarily, per protocol/treatment. The per protocol analysis is aimed at patients completing the study protocol as initially assigned, without significant breach or crossover, whereas the per treatment analysis addresses the treatment modality received, regardless of initial device assignment. Per protocol/treatment analyses are intended solely for descriptive comparisons, not as tests of the working hypothesis. For the intention-to-treat analysis, all patients giving written informed consent and randomly assigned for the study will be used in the analysis sample, whether or not the treatment rendered was correct or crossover occurred. The endpoints will also be subjected to per patient and per lesion analyses as feasible.

The null hypothesis will be evaluated on a non-inferiority basis, using an independent sample t-test of the mean late lumen loss in both groups. Non-inferiority is defined by a one-sided alpha of 5% and a difference in late lumen loss ≤0.2 mm. TLF, TLR, TVR, MI and stent thrombosis rates at 12 months will be analyzed with a χ2-test, generating Kaplan–Meier survival estimates for time to events of TLF, TLR, TVR and MI at 12 months. Acute success (device, lesion and procedure) analysis will utilize a χ2-test as specified. An independent t-test or χ2-test will be invoked as needed to assess in-stent/in-segment %DS and in-stent/in-segment binary restenosis at 9 months. In addition, exploratory subgroup analysis will be performed, rather than pre-specified subgroup analysis.

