## Methods/design

### Study design

This is a prospective, randomized, open-label, and parallel-group multicenter trial designed to test the non-inferiority of the Orsiro SES relative to the ZES-I in preventing late lumen loss 9 months after the index procedure (Figure 1). A total of 375 patients exhibiting a wide spectrum of CAD will be enrolled at eight centers in Korea. Participants will be monitored clinically at months 1, 6, 9 and 12. Investigators may conduct this follow-up as telephone interviews or office visits. An angiographic follow-up to determine late lumen loss is advised at 9 months post-procedure or earlier should the patient experience ischemic symptoms or show non-invasive evidence of ischemia.

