### Study population and entry criteria

Prospective subjects are those at least 18 years of age, presenting with symptomatic CAD (including acute coronary syndrome) and coronary lesions >50%, in whom PCI with DES implantation is indicated, based on the current recommendations of ACC/AHA/SCAI and ESC/EACTS guidelines or the clinical judgment of the interventional cardiologist (Table 1) [8,9]. Whether the PCI is indicated based on current recommendations or not will be separately recorded. Inclusion and exclusion criteria will be graded to minimize exclusion of patients, thus reflecting the population at large. All participants will be randomly assigned in a 2:1 ratio to either the Orsiro SES or ZES-I group. To generate comparable groups relative to known and unknown risk factors, randomization will be independently conducted online via a web-based application (T&W Software, Seoul, Korea). The randomization will be balanced and stratified by participating center and allocated treatment groups.

**Table 1 T1:** Eligibility criteria for the ORIENT trial

**Inclusion criteria**	● Patient age ≥18 years
	● Ability to acknowledge verbally the risks, benefits and treatment ramifications in receiving the Orsiro Hybrid® or Resolute Integrity® stent
	● Written informed consent given by legally authorized agent prior to any study-related procedure
	● Indication for use of drug-eluting stent based on ACC/AHA/SCAI and ESC/EACTS guidelines and/or clinical judgment of interventional cardiologist.
	● Target lesion(s) in coronary artery or graft vessel with estimated reference diameter ≥2.5 mm and ≤5.0 mm
	● Target lesion(s) amenable to percutaneous coronary intervention
**Exclusion criteria**	● Known hypersensitivity or contraindication to any of the following agents: heparin, aspirin, clopidogrel, sirolimus, zotarolimus, cobalt chromium or contrast media^a^
	● Inability to tolerate aspirin or clopidogrel for 1-year duration of study
	● Systemic (intravenous) use of sirolimus or zotarolimus within 12 months
	● Females with childbearing potential (unless negative by a recent pregnancy test) or anticipating pregnancy following study enrollment
	● History of bleeding diathesis, known coagulopathy (including heparin-induced thrombocytopenia), or refusal of blood transfusions
	● Gastrointestinal or genitourinary bleeding within prior 3 months, or major surgery within 2 months
	● Planned major non-cardiac surgery within designated study period

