### Quantitative coronary angiography

The coronary angiography at baseline, immediately after the procedure and at follow-up will be analyzed using an automated edge-detection system (Cardiovascular Angiography Analysis System 5.7.1; Pie Medical Imaging Systems, Maastricht, the Netherlands) at the core laboratory in Seoul National University Bundang Hospital by an experienced technician who is blinded to the study. The minimal lumen diameter (MLD), reference vessel diameter, %DS, acute gain (difference in MLD pre- and post-implantation of the stent), late lumen loss (difference in post-procedural and follow-up MLD) and binary restenosis (≥50% stenosis at the follow-up angiography) will be measured [13]. All QCA assessments of target lesions will be in-stent and in-segment (stent plus 5-mm proximal and distal margins).

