### Statistical considerations

#### Sample size calculation

To test the primary hypothesis (non-inferiority of the Orsiro SES relative to the ZES-I by 9-month in-stent late lumen loss), we assumed a mean late loss of 0.3 mm (SD 0.54 mm) for both stents, which was extrapolated from the QCA results for the Endeavor Resolute® (ZES-R) from the RESOLUTE US trial [14]. The ZES-I and ZES-R devices use same the delivery drug (zotarolimus) and basic design, namely a biocompatible polymer (BioLinx®) mounted on a cobalt chromium platform. For non-inferiority testing, with a 0.2 mm non-inferiority margin, type I error at 0.05 (one-sided), 90% statistical power, 2:1 sampling ratio (Orsiro SES:ZES-I) and an expected 30% dropout rate (at the 9-month follow-up angiography), a total of 375 patients (Orsiro SES, 250; ZES-I, 125) were deemed necessary to execute this study. To avoid interlesion clustering of restenosis in patients receiving stents for multiple lesions, which would have required correction with multilevel generalized estimating equations, only one randomly selected lesion will be used in the analysis of in-stent late lumen loss [15,16]. Sequential superiority testing will be performed if non-inferiority for in-stent late lumen loss is met. This number of patients would also have 92% power to detect superiority with an in-stent late lumen loss difference of 0.2 mm between the groups at a two-sided alpha level of 0.05.

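### The primary t-test ignores the stratifying centre and the pre-procedural QCA already collected: it is valid, but less efficient than it could be

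*Protocol article*

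**What the plan says.** The Statistical analysis section of the Protocol article fixes the primary comparison: the null hypothesis is evaluated "using an independent sample t-test of the mean late lumen loss in both groups". It names no stratified or covariate-adjusted version, and does not say whether the variance is pooled.

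Three other sections bear on this choice:

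- **Study population and entry criteria:** "The randomization will be balanced and stratified by participating center and allocated treatment groups". A treatment group cannot be a stratum for its own allocation, so centre is the only usable stratification factor stated. Study design says that patients "will be enrolled at eight centers in Korea".
- **Quantitative coronary angiography:** "The coronary angiography at baseline, immediately after the procedure and at follow-up will be analyzed" by the core laboratory. The measurements include MLD and reference vessel diameter. The pre-procedural MLD must exist, because the section also derives "acute gain (difference in MLD pre- and post-implantation of the stent"). The endpoint itself is "late lumen loss (difference in post-procedural and follow-up MLD"), so pre-procedural values do not enter it.
- **Sample size calculation:** "we assumed a mean late loss of 0.3 mm (SD 0.54 mm) for both stents", "with a 0.2 mm non-inferiority margin". The SD is not reduced for any covariate, which is consistent with an unadjusted test.

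**The concern.** Stratifying by centre balances the arms within centre. If centres differ in late loss, the true sampling variance of the treatment difference is then smaller than under simple randomisation. A t-test that ignores centre still leaves the between-centre variation in its standard error, so that standard error is somewhat too large. Separately, the pre-procedural vessel measurements precede stent placement and could absorb part of the residual variance, but the stated test does not use them.

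What is at stake is precision. The confidence limit compared with 0.2 mm may be wider than the collected data require, for both the non-inferiority test and the superiority test that follows it.

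**Working it through.** **Inputs from the Protocol article (Sample size calculation):** SD 0.54 mm in both arms, true difference 0, margin 0.2 mm, one-sided alpha 0.05, 375 patients as 250 + 125, 30% angiographic loss. Evaluable: 250 × 0.7 = 175 and 125 × 0.7 = 87.5, about 262.

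**Assumption not in the article:** R², the share of late-loss variance explained by centre and pre-procedural QCA. Range shown: 0 to 0.15.

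**1. The plan's own figures.** Evaluable control patients for 90% power: (1.645 + 1.282)² × 0.54² × 1.5 / 0.2² = 93.6, so 94, or 282 in total. Dividing by 0.7 gives 403, not 375. The stated 92% superiority power reproduces only with all 375 analysed (SE 0.0592 mm, power 92.2%). Both are separate matters; they are noted here only to fix the starting point.

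**2. Unadjusted test with 262 evaluable.** SE = 0.54 × √(1/175 + 1/87.5) = 0.0707 mm.

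- Non-inferiority: Φ(0.2/0.0707 − 1.645) = Φ(1.184) = 88.2%.
- Superiority at a 0.2 mm difference: Φ(0.2/0.0707 − 1.960) = Φ(0.869) = 80.8%.

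**3. Adjusted analysis.** The SE is multiplied by √(1 − R²).

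| R² | SE (mm) | Non-inferiority power | Superiority power |
|---|---|---|---|
| 0 | 0.0707 | 88.2% | 80.8% |
| 0.05 | 0.0689 | 89.6% | 82.7% |
| 0.10 | 0.0671 | 90.9% | 84.7% |
| 0.15 | 0.0652 | 92.3% | 86.6% |

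An R² of about 0.066 would bring 262 evaluable patients to 90% non-inferiority power.

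**4. Centre alone.** Suppose centre explains a share ρ of the variance and is balanced by design. The one-sided size of the unadjusted test is then 1 − Φ(1.645/√(1 − ρ)). Its power is Φ(1.184/√(1 − ρ)).

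| ρ | True size of t-test | Power, t-test | Power, centre in model |
|---|---|---|---|
| 0.02 | 4.8% | 88.4% | 88.7% |
| 0.05 | 4.6% | 88.8% | 89.6% |
| 0.10 | 4.1% | 89.4% | 90.9% |

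So the part of R² that comes from centre buys only 0.3, 0.8 or 1.5 points, because stratification has already delivered some of the benefit. These figures assume that balance within centre survives the 30% loss. It will do so only in part, so the conservatism is at most this large.

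**5. Cost if the covariates explain nothing.** For seven centre terms plus one covariate, the change in the t critical value costs less than 0.01 point. Chance imbalance adds a little: for k covariates not balanced by design, the variance grows by a factor of about 1 + k/(n − k − 3).

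- The two QCA covariates only: 1 + 2/257.5 = 1.008, power 88.0%.
- Centre terms also treated as unbalanced (the worst case), k = 9: 1 + 9/250.5 = 1.036, power 87.2%.

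The loss at R² = 0 is therefore about 0.2 to 1.0 point. The table in step 3 leaves out this small cost.

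**The case against.** The strongest reply is that nothing here is an error. An unadjusted t-test is a valid test of the stated hypothesis and matches the sample size calculation. A standard error that is slightly too large makes non-inferiority harder to claim, which is the safe direction. That stands in full.

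Nor does the article show that the covariates are prognostic. Pre-procedural MLD is not a baseline value of late loss, so the usual argument for a large gain from baseline adjustment does not carry over, and a gain near zero cannot be excluded. That also stands, and is why the range starts at zero. What it leaves untouched is the asymmetry: the possible gain is several points, and the possible loss is at most about one.

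A reader might infer something stronger: that with 2:1 allocation the t-test exceeds its one-sided 5% level. With evaluable arms of 175 and 87, a pooled-variance test has size 6.7% if the SDs are 0.45 mm (Orsiro) and 0.60 mm (ZES-I). With the SDs reversed, it is 3.5%. The article supports neither case. It does not say that the variance is pooled, it assumes 0.54 mm for both stents, and it gives no reason to expect more variation in the smaller arm. Choosing between pooled and Welch forms is also detail that an analysis plan commonly settles.

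The shortfall against the stated 90% power is a sample size question with its own remedy. It makes precision more welcome, but it does not make the t-test wrong.

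**Conclusion.** The point holds as a modest improvement in efficiency. The stated primary test is valid and, after stratification by centre, slightly conservative. The article supports neither an inflated type I error nor a biased comparison.

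The gain rests on an R² that the article does not give. Over R² from 0 to 0.15, with 30% loss and SD 0.54 mm, it runs from nothing to about 4 points of non-inferiority power (88.2% to 92.3%) and about 6 points of superiority power (80.8% to 86.6%). It is smaller to the extent that centre supplies the R². The recommendation does not depend on a particular value, because the cost is small even at zero.

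**What to change.** Replace the sentence naming the primary test, before any follow-up angiographic data are seen, so that the covariates cannot be chosen on the results:

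- **Primary analysis:** a linear model for in-stent late lumen loss with treatment, centre, pre-procedural reference vessel diameter and pre-procedural MLD. Declare non-inferiority if the upper one-sided 95% confidence limit for the adjusted Orsiro minus ZES-I difference is below 0.2 mm.
- **Sensitivity analysis:** the unadjusted t-test.
- **Do not adjust** for post-procedural MLD or acute gain. Both are measured after the assigned stent is placed, and post-procedural MLD is part of the endpoint.
- **Standard errors:** given 2:1 allocation, state unequal-variance forms (Welch for the t-test, robust for the model) as an inexpensive safeguard.

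If a full analysis plan already contains an adjusted primary analysis, the two texts need only be aligned.

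The cost is a change of wording, seven degrees of freedom for eight centres and one for each covariate. No new patients, visits or measurements are needed.

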### Outcome measurements and definitions

The primary endpoint of the trial is in-stent late lumen loss at 9 months, as measured by quantitative coronary angiography (QCA). Secondary angiographic endpoints at 9 months are in-segment late lumen loss, percentage diameter stenosis (%DS) and binary restenosis. Secondary clinical endpoints include all-cause and cardiac deaths, clinically driven target lesion revascularization (TLR), target vessel revascularization (TVR), myocardial infarction (MI) (target or non-target vessel-related), stent thrombosis and target lesion failure (TLF, a composite of cardiac death, TLR and target vessel-related MI) at 12 months [10,11]. Revascularization is considered clinically driven if the follow-up angiographic diameter stenosis ≥50%, and there is at least one of the following: (1) history of recurrent angina pectoris, presumably related to the target vessel, (2) objective signs of ischemia at rest or during exercise testing (or equivalent), presumably due to the target vessel, (3) abnormal invasive functional diagnostic testing or (4) TLR or TVR with ≥70% diameter stenosis, even without any of the aforementioned ischemic signs/symptoms [10,12].

To reduce the chance of the so-called oculostenotic reflex, whereby rates of repeated revascularization are disproportionately high, investigators will be encouraged to perform a non-invasive stress test or invasive functional diagnostic test (for example, fractional flow reserve) prior to a decision regarding repeated revascularization and they will adhere strictly to a clinically driven revascularization protocol. In addition, the specified indication of revascularization and the number of TVRs or TLRs that are performed without a non-invasive stress test will be separately recorded.

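### Sparse 12-month events, above all stent thrombosis, are to be compared by a χ2-test with a 125-patient comparator arm, where an uncorrected test can call two events against none significant for Orsiro (minor)

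*Protocol article*

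**What the plan says.** In the protocol article, under Statistical analysis: "TLF, TLR, TVR, MI and stent thrombosis rates at 12 months will be analyzed with a χ2-test". The same sentence adds Kaplan–Meier "survival estimates for time to events of TLF, TLR, TVR and MI at 12 months". Stent thrombosis is in the first list but not the second, so the χ2-test is the only analysis named for it. The sentence does not say whether a continuity correction applies and gives no rule for small expected counts.

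The arm sizes are in Sample size calculation: "a total of 375 patients (Orsiro SES, 250; ZES-I, 125) were deemed necessary to execute this study". Secondary endpoints are analysed first by intention to treat, so clinical events are compared in about 250 v 125 patients. The 30% dropout in that section refers to the 9-month angiography. The article gives no expected clinical event rates and no alpha level for these comparisons. The only two-sided level it states is for late-loss superiority: "between the groups at a two-sided alpha level of 0.05".

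**The concern.** The χ2 approximation needs adequate expected counts. With 2:1 allocation the smaller arm receives a third of the events, so a rare endpoint quickly falls below the usual threshold of 5. The failure is also asymmetric: a couple of events in the small comparator arm can produce a low p-value, whereas the same number in the larger Orsiro arm cannot.

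This matters because thrombosis is part of the trial's rationale. The Background describes thrombogenic risk as the price of drug-eluting stents, and the Discussion attributes lower thrombogenicity to the Orsiro coating. A p-value below 0.05 for stent thrombosis resting on two events could be read as evidence of a safety advantage.

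**Working it through.** **Inputs.** Arm sizes 250 and 125 come from Sample size calculation (375 × 2/3 = 250; 375 × 1/3 = 125). Two-sided alpha 0.05 is an assumption, since none is stated for these endpoints. Event rates are also assumed: equal in both arms, over a range of 0.2% to 5%. The plan gives no figure for these comparisons, so there is none to reproduce.

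**Step 1, expected counts.** With m events in total, the expected ZES-I count is m × 125/375 = m/3. This reaches 5 at m = 15, a pooled rate of 15/375 = 4%.

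**Step 2, single tables.** For events a of 250 (Orsiro) and c of 125 (ZES-I), with non-events b and d:

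χ2 = N(ad − bc)² / [250 × 125 × (a + c) × (b + d)]

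- 0/250 v 2/125: 375 × 500² / (250 × 125 × 2 × 373) = 4.02, p = 0.045. The expected ZES-I count is 2/3 = 0.67.
- The same table with Yates' correction: 375 × (500 − 187.5)² / (250 × 125 × 2 × 373) = 1.57, p = 0.21.
- The same table by Fisher's exact test: (125 × 124)/(375 × 374) = 0.1105. The mid-p value is half of this, 0.055.
- 7/250 v 0/125: 375 × 875² / (250 × 125 × 7 × 368) = 3.57, p = 0.059.
- 8/250 v 0/125: 375 × 1000² / (250 × 125 × 8 × 367) = 4.09, p = 0.043.
- 3/250 v 6/125: Pearson p = 0.032, Fisher 0.065, Yates 0.074.

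So with no events in the other arm, two ZES-I events suffice for a result favouring Orsiro, while eight Orsiro events are needed for a result against it. Attrition does not change the first result: 0/240 v 2/120 also gives p = 0.045.

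**Step 3, error rates under equal true rates.** For each rate p, the binomial probabilities of a (n = 250) and c (n = 125) are multiplied and summed over all tables with a p-value below 0.05.

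| Assumed rate, both arms | Expected ZES-I events | Pearson, favours Orsiro | Pearson, against Orsiro | Fisher, total |
|---|---|---|---|---|
| 0.2% | 0.25 | 1.6% | 0.0% | 0.1% |
| 0.5% | 0.63 | 3.85% | 0.0% | 0.9% |
| 0.8% | 1.0 | 4.15% | 0.04% | 1.7% |
| 1% | 1.25 | 3.9% | 0.1% | 2.1% |
| 2% | 2.5 | 3.0% | 1.2% | 3.0% |
| 5% | 6.25 | 2.9% | 1.9% | 3.8% |

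At 0.5%, the single table 0 v 2 has probability 0.995^250 × 7750 × 0.005² × 0.995^123 = 0.030. It therefore supplies most of the 3.85%.

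**Step 4, after the change.** Under Fisher's test the first significant table favouring Orsiro with no Orsiro events is 0 v 3 (p = 0.036). The first against it with no ZES-I events is 9 v 0 (p = 0.032; 8 v 0 gives 0.056).

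**The case against.** The strongest objection is that this is one sentence in a condensed article, and that switching to an exact test when counts are small is routine detail for the analysis plan or the software. That has force, and it lowers the weight of the point. But the article does more than leave the matter open: it names a test for an endpoint likely to be sparse, and for stent thrombosis it names no other analysis.

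The second objection is that the headline table depends on the form of the test. This stands. With Yates' correction 0 v 2 gives p = 0.21, and the article does not say which form is meant. The alpha is assumed as well.

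A reader might also infer more than the document supports:

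- **That type I error is inflated overall.** It is not. The Pearson total stays below 5% at every rate examined (1.6% at a 0.2% event rate, up to 4.9% at 5%). The fault is where the error falls.
- **That χ2 is wrong for TLR, TVR and TLF too.** No event rates are given, and at a pooled rate of 4% or more the test is acceptable. Death is not in the χ2 sentence at all.
- **That pairing χ2 with Kaplan–Meier curves is an error, to be cured by a log-rank test.** Reporting crude 12-month rates beside curves is common practice. Clinical follow-up may be by telephone, so large clinical losses are not shown. The log-rank test shares the sparse-count fault: with complete follow-up, 0 v 2 again gives about 4.02, p = 0.045.

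**Conclusion.** The point holds in a narrow form. For stent thrombosis, and for MI or another listed event if it yields fewer than 15 events in total, the named χ2-test is unreliable at 250 v 125. If applied without correction at two-sided 0.05, it calls 0 v 2 significant for Orsiro but needs 8 v 0 against it. At assumed equal rates of 0.5% to 1%, about 3.9% to 4.2% of trials would show a false advantage for Orsiro, against a nominal 2.5% per side, and at most 0.1% a false disadvantage.

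The result rests on an uncorrected test, an assumed alpha and assumed event rates. It concerns secondary endpoints only. The sample size and formal hypothesis are about late lumen loss, and the article plans no formal safety claim from these tests. The point is minor.

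**What to change.** Amend the sentence in Statistical analysis. For stent thrombosis, and for any 12-month event endpoint with an expected cell count below 5 (possibly MI), replace the χ2-test with Fisher's exact test or an exact mid-p test, naming one in advance. Report an exact confidence interval for the risk difference alongside. Keep χ2 for commoner endpoints, state whether a continuity correction is used, and state the alpha for these comparisons. The Kaplan–Meier estimates can stay as they are.

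The change costs wording only, with no extra patients or data. Fisher's test is conservative (total error 0.9% at a 0.5% rate, 2.1% at 1%). It also does not restore sensitivity against Orsiro, since 9 v 0 is then needed. That limit comes largely from the 2:1 allocation and is why the interval matters as much as the p-value. Mid-p is less conservative: Fisher's p less half the observed table's probability gives 0.055 for 0 v 2, but 0.0653 − 0.0329/2 = 0.049 for 3 v 6. The choice should therefore be fixed before the data are seen.

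### The χ2-test named for stent thrombosis and the other 12-month event rates gives unreliable p-values at the small counts expected for the rarest outcomes; an exact test should replace it when the table is sparse

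*Protocol article*

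**What the plan says.** Under Statistical analysis, the article says: "TLF, TLR, TVR, MI and stent thrombosis rates at 12 months will be analyzed with a χ2-test". For procedural outcomes it says: "Acute success (device, lesion and procedure) analysis will utilize a χ2-test as specified". It also names the χ2-test, as needed, for binary restenosis at 9 months. No continuity correction, expected-count rule or exact test is mentioned.

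Kaplan–Meier curves are planned as "survival estimates for time to events of TLF, TLR, TVR and MI at 12 months". Stent thrombosis is not in that list, so the χ2-test is its only named analysis.

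Under Sample size calculation, "a total of 375 patients (Orsiro SES, 250; ZES-I, 125) were deemed necessary". The intention-to-treat rule is that "all patients giving written informed consent and randomly assigned for the study will be used in the analysis sample", so the denominators for the clinical rates are 250 and 125. The article gives no expected event rate and no significance level for the clinical endpoints.

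**The concern.** The χ2-test relies on a large-sample approximation, commonly trusted when every expected cell count is at least about 5. Stent thrombosis is the outcome most likely to break that condition here, because the comparator arm has only 125 patients.

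The Background and Discussion present stent thrombosis as a main reason for developing newer stents, so a p-value on it will be noticed. If the stated test is followed literally, two events can be reported as a significant difference between stents when an exact calculation finds nothing unusual.

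**Working it through.** **Inputs.** 250 and 125 patients (Sample size calculation); all randomized patients analysed and the χ2-test named (Statistical analysis). Assumed here: uncorrected Pearson χ2, as the plain reading of the text; two-sided 0.05; and common event rates of 0.5% to 2%. The article gives no figure for these tests to reproduce. The split itself checks: 375 × 2/3 = 250 and 375 × 1/3 = 125.

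**1. When the table is sparse.** With m events in total, the pooled expected ZES-I count is m × 125/375 = m/3. This is below 5 when m < 15, and 15/375 = 4%.

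**2. Two events, both on ZES-I.** Pearson χ2 = N(ad − bc)² / (product of the four margins), with a = 0, b = 250, c = 2, d = 123:

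375 × 500² / (250 × 125 × 2 × 373) = 4.02, p = 0.045.

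With no stent effect, the exact chance of this split given two events is (125/375) × (124/374) = 0.1105. That is also Fisher's two-sided p, because every other split of two events is more probable. A Yates correction would give p = 0.21.

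**3. All events in one arm.** The formula reduces to 187.5m/(375 − m) when all m events are on Orsiro:

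| Orsiro vs ZES-I events | χ2 | Pearson p | Fisher p |
|---|---|---|---|
| 2 vs 0 | 1.01 | 0.32 | 0.55 |
| 7 vs 0 | 3.57 | 0.059 | 0.10 |
| 8 vs 0 | 4.09 | 0.043 | 0.056 |
| 9 vs 0 | 4.61 | 0.032 | 0.032 |

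On the other side, 0 vs 3 gives Fisher p = (125 × 124 × 123)/(375 × 374 × 373) = 0.036, so it is significant under both tests.

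**4. False-positive rates.** These come from enumerating two independent binomials (250 and 125) with equal true rates:

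| Assumed rate | χ2 favours Orsiro | χ2 favours ZES-I | χ2 total | Fisher favours Orsiro |
|---|---|---|---|---|
| 0.5% | 3.9% | <0.01% | 3.9% | 0.9% |
| 0.75% | 4.2% | 0.03% | 4.2% | 1.5% |
| 1% | 3.9% | 0.11% | 4.0% | 2.1% |
| 2% | 3.0% | 1.2% | 4.2% | 2.5% |

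**5. Where the two tests disagree.** Among all tables with fewer than 15 events, the verdict at 0.05 changes in four: 0 vs 2, 3 vs 6, 8 vs 0 and 12 vs 1. Each is significant by Pearson and not by Fisher.

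The 0 vs 2 table accounts for nearly all of the gap in step 4. Its unconditional probability is C(125,2) p²(1 − p)³⁷³, with C(125,2) = 7750. At 0.5% this is 7750 × 0.005² × 0.995³⁷³ = 3.0%, and 3.9% − 0.9% = 3.0%. At 1% it is 1.8%, against a gap of 3.9% − 2.1% = 1.8%.

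**The case against.** **A level-5% test is not broken.** The total two-sided error of the χ2-test stays below 5% at every rate examined (2.6% to 4.9% for rates of 0.3% to 8%). The 11% figure is conditional on exactly two events, and the 0 vs 2 table occurs in at most about 3% of null trials at the rates in step 4. This stands. What remains is an excess in one tail of 1.4 to 1.7 percentage points and a misleading p-value in particular tables.

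**The asymmetry is not caused by the χ2-test.** A reader might infer that the test choice biases the safety comparison toward Orsiro and that an exact test would cure this. The design figures do not support that reading. With few events and 2:1 allocation, any test reaches significance sooner when events fall in the smaller arm. Of the chance significant results at a 1% rate, 97.1% favour Orsiro under χ2 and 98.6% under Fisher; at 2% the shares are 72% and 81%. Fisher's test also makes a signal against Orsiro slightly harder to reach. This stands in full.

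**It is routine detail in a condensed article.** A full analysis plan may already hold a small-count rule. That is possible, and one should be confirmed if it exists. But the article does not leave the test open. It names one, and for stent thrombosis names nothing else.

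**The consequence is limited.** These are secondary endpoints with no stated alpha or claim attached, and the article provides for event adjudication and a data safety and monitoring board. This stands, and limits how much weight the point deserves.

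**Conclusion.** The point holds for sparse tables. Following the stated test for stent thrombosis, 0 vs 2 events would be reported as p = 0.045 when the exact value is 0.11. At assumed rates of 0.5% to 1% the χ2-test falsely favours Orsiro in 3.9% to 4.2% of trials, where Fisher's test does so in 0.9% to 2.1%.

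The size depends on three things the article does not give: the event rate, the significance level for the clinical endpoints, and whether a continuity correction applies. The worked harm is confined to outcomes at about 1% or below. It should not be extended to TLF, TLR, TVR or a commoner MI rate; at 5% the two tails under χ2 are already 2.9% and 1.9%. All-cause and cardiac death are outside the quoted list.

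The figures do not show inflated overall type I error, and they do not show a directional bias peculiar to the χ2-test. This is a secondary-endpoint correction, worth making because it is nearly free and should be settled before outcomes are known.

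**What to change.** In Statistical analysis, replace the χ2-test for 12-month event rates, acute success and binary restenosis with wording such as:

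*Fisher's exact test will be used when any expected cell count, computed from the pooled data, is below 5, and always for stent thrombosis; otherwise the χ2-test. The risk difference will be reported with an exact or score-based 95% confidence interval.*

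For sparse tables the interval should be exact, with 2.5% in each tail. A score interval is the counterpart of the Pearson test, and for 0 vs 2 events it excludes zero just as the Pearson p-value falls below 0.05.

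The cost is a sentence or two, with no extra patients or data. The downsides should be stated with the change. Fisher's test is conservative at low counts, it leaves the asymmetry from 2:1 allocation in place, and it needs 9 vs 0 rather than 8 vs 0 events for a significant result against Orsiro. A non-significant p-value must therefore not be read as evidence of safety; the confidence interval should carry that conclusion.
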